## Methods and analysis

### Study design and participants

This clinical feasibility study involves the recruitment of 30 participants with clinically diagnosed PD at the Center for Neurology, Academic Specialist Center Torsplan (ASCT), Stockholm Health Services, Region Stockholm.

Participants are recruited based on the inclusion and exclusion criteria summarised in table 1. Guided by similar studies that have used between 10 and 50 participants,^18–20^ the goal of this study is towards hypothesis generation and assessing feasibility. Efforts are made to recruit participants with a diverse range of PD symptoms while avoiding over-representation of one sex or age category. Given the limited number of participants and the exploratory nature of this study, no specific software is used for randomisation; an ad hoc approach is adopted depending on the circumstances. Recruitment started in the fourth quarter of 2022, with plans to complete data collection in the fourth quarter of 2023.

**Table 1 T1:** Inclusion/exclusion criteria

Inclusion criteria	Exclusion criteria
Must be diagnosed with Parkinson’s disease and under treatment at Karolinska University Hospital or Academic Specialist Center Torsplan	Not able to use a smartphone independently
Must have mild or moderate motor and non-motor symptoms	Unable to read and understand Swedish
Must own a smartphone, Android or iPhone	Severe symptoms (H&Y 3 and above)

H&Y, Hoehn and Yahr.

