#### Validity of measurements collected by mobile phones and wearables

From the data collected from activity tests and the wrist-wearable device, we will extract features and train machine learning models to infer the severity of the disease using the MDS-UPDRS score as a reference. This includes measuring time needed to complete the TUG test, finger dexterity in the FT test, tremor in the HTP and the drawing tests, and assessing voice distortions in the vocalisation test.^31^ The main metric for assessing validity will be correlation between features and/or inferred scores and actual scores. We will associate the measurements to the MDS-UPDRS closest in time. The variability of fluctuating symptoms will be addressed by exploring how averaging features, including before and after medication and over the weeks, affects the correlation. The data collected by the wearable will also offer a reference to understand if and in what way symptoms have evolved over time.

As targets, we will employ both summative scores, for example, for part 3 (motor symptoms), which will be compared with aggregated results from all the tests, and specific items, when those can be mapped to the result of a specific test, for example, finger tapping with item 3.4.

Data acquired by the GWALK gait analysis device during the TUG tests in clinic will be employed as a reference to validate the algorithms used to analyse the data collected by the app in the same test.

Algorithms will be implemented to assess tremor, bradykinesia and sleep quality from the actigraphy data obtained from the wearable device. Sleep-related questionnaires will serve as a reference for sleep quality assessment.

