Various machine learning classifiers such as AdaBoost, random forest, multilayer perceptron, support vector machine, XGBoost and similar algorithm for regression analysis will be trained to predict symptoms scores. Regression models will be used to predict the scale of the MDS-UPDRS whereas classifiers will be used to predict scores binned into boarder categories (eg, no symptoms, low symptoms, high symptoms). A preliminary proof of feasibility has been performed through a regression analysis to infer disease severity^32^ based on a dataset with self-reported part of MDS-UPDRS components collected in the mPower study.^33^ This offered insights into the anticipated quality from data collected in free-living conditions. Importantly, a correlation between data collected from smartphones and symptoms’ severity was confirmed but only after removing a substantial number of participants who were considered unreliable. This study aims to address those deficiencies by selectively recruiting participants with clinically diagnosed PD.

Algorithms for classification and regression analysis will be compared on different evaluation metrics including common performance metrics such as accuracy, sensitivity, specificity and area under the curve-receiver operating characteristic (AUC-ROC) for classifiers. For regression models, metrics like mean squared error, mean absolute error and R square measures will be used.

Feature selection (FS) will be performed, and the best predictive features will be identified. Methods mentioned in,^34^ Relevance, Redundancy, and Complementarity Trade-off, minimal-redundancy-maximal-relevance (mRMR Peng), correlation-based FS and recursive feature elimination will be explored, as well as dimensionality reduction techniques such as principal component analysis.^35^ To assess the performance of different machine learning algorithms, k-fold cross-validation and leave-one-participant-out cross-validation method will be used, in order to account for participant identity confounding.

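### With 30 participants, any best learner, feature set or averaging scheme picked on the folds that score it will look too good, and participant-wise folds do not prevent this

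*Protocol article*

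**What the plan says.** All of this comes from the protocol article.

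- **Size and purpose** (Study design and participants). "This clinical feasibility study involves the recruitment of 30 participants with clinically diagnosed PD". The number rests on precedent: "Guided by similar studies that have used between 10 and 50 participants". The same sentence gives the purpose: "the goal of this study is towards hypothesis generation and assessing feasibility".
- **Validity metric** (Validity of measurements collected by mobile phones and wearables). "The main metric for assessing validity will be correlation between features and/or inferred scores and actual scores".
- **Averaging** (same section). Fluctuating symptoms are handled by "exploring how averaging features, including before and after medication and over the weeks, affects the correlation".
- **Targets** (same section). Both summary scores, such as part 3, and single items, such as 3.4 for finger tapping, serve as targets.
- **Learners** (same section). The open list is "AdaBoost, random forest, multilayer perceptron, support vector machine, XGBoost and similar algorithm for regression analysis". "Algorithms for classification and regression analysis will be compared on different evaluation metrics", and no metric is named as the deciding one.
- **Features** (same section). "Feature selection (FS) will be performed, and the best predictive features will be identified". Four selection methods and principal component analysis are to be explored.
- **Cross-validation** (same section). K-fold and leave-one-participant-out are both named for assessing the algorithms' performance. The only reason given is identity confounding.

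No held-out or external test set is named. The mPower data appear only as preliminary feasibility work.

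**The concern.** Participant-wise folds stop one person's recordings from appearing in both training and test data. They do nothing about a second source of optimism. When many pipelines are scored on the same folds and the highest score is kept, that score includes the luck that made it highest.

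The plan opens several routes to this: the learner, the selection method, the number of features kept and the averaging scheme. Averaging is the plainest case, because its effect is to be studied on the validity metric itself. The article names identity confounding as the threat that cross-validation answers and does not mention selection optimism.

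At stake are the first two research questions under Outcomes: whether the measurements are valid for estimating symptoms, and which features predict MDS-UPDRS scores. With 30 participants, an inflated correlation could be taken as evidence of validity, and a list of best features could contain names that a second sample would not return.

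**Working it through.** The article gives no power, precision or accuracy figure to reproduce. The check is therefore how large a cross-validated correlation appears when no feature carries any information.

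**Inputs from the article.** n = 30, one group. At least five learners. Several averaging schemes, number not given. Correlation as the main metric. Participant-wise cross-validation.

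**Assumptions, not in the article.**
- 50, 100 or 200 candidate features, one row per participant, and a score independent of all of them.
- Four averaging schemes with a correlation of 0.6 between versions of a feature.
- Five learners as stand-ins: ridge at three penalties and nearest neighbours at two sizes.
- Five or ten features kept by univariate correlation.
- Pipelines: 4 schemes × 5 learners × 2 feature counts = 40.
- 10-fold participant-wise cross-validation, 300 runs per setting.

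**Yardstick.** The nominal two-sided 5% value of r at n = 30 is t/√(28 + t²) with t = 2.048 on 28 degrees of freedom: 2.048/√(28 + 4.194) = 2.048/5.674 = 0.361.

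**Results with true correlation 0.**

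| What is done | 50 features | 100 features | 200 features |
|---|---|---|---|
| One pipeline fixed in advance, selection inside folds: mean r (mean R²) | −0.08 (−0.36) | −0.05 (−0.34) | −0.05 (−0.36) |
| Best of 40, selection inside folds: mean r (mean best R²) | 0.31 (0.07) | 0.34 (0.10) | 0.34 (0.10) |
| Same, 95th percentile of r | 0.56 | 0.61 | 0.61 |
| Same, share of runs with r above 0.361 | 41% | 48% | 48% |
| One pipeline, features selected once on all 30: mean r (mean R²) | 0.48 (0.23) | 0.59 (0.35) | 0.64 (0.41) |
| Best of 40, features selected once on all 30: mean r | 0.66 | 0.74 | 0.79 |

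The simulation error on the shares is about √(0.48 × 0.52/300) = 0.029, or 3 percentage points.

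**Full nesting.** A separate null run with 50 to 100 features and 40 pipelines gave a best-of-40 mean r of about 0.33, above 0.361 in 40% to 42% of runs. When the pipeline was instead chosen inside each training set and the outer folds only scored it, mean r was about −0.08 to −0.02.

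**Selection on all data under leave-one-participant-out.** Ridge on the top 5 of 50, 10 of 100 and 10 of 200 null features (200 runs each) gave mean r of 0.48, 0.62 and 0.69, and R² of 0.22, 0.37 and 0.47. Redoing the selection inside each training set gave r of −0.08 to −0.03.

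**No model at all.** The largest absolute correlation of a single null feature with the score has a median of 0.35 for 10 features, 0.45 for 50, 0.48 for 100 and 0.52 for 200.

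The second to fourth rows of the table carry the point. They use correct in-fold feature selection and participant-wise folds, and the optimism remains. It comes only from keeping the best of many.

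**The case against.** The strongest reply is that a condensed article is being read as if its silences were decisions. It names k-fold and leave-one-participant-out without saying how they are arranged, and an inner and outer loop is compatible with the wording. It does not put feature selection outside the folds. It says learners will be compared, not that only the winner is reported. Exploring averaging schemes can be read as a sensitivity analysis. The study calls itself hypothesis-generating and lists sample size as a limitation. Some targets are tied to a specific test, so screening a hundred noise features is a harsh model for them.

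Most of this stands, and it rules out the stronger readings that a reader might infer:

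- That features are selected once on all participants. The article does not say so, so values of about 0.5 to 0.7 are conditional on an unstated choice.
- That there is only one layer of cross-validation, that an averaging scheme will be chosen, or that a single winner will be reported. None of these is stated.
- That the feature question will be answered largely by chance. This assumes no true signal, which is the simulation's premise and not a fact about the study.

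What does not fall is the conditional point. The text does commit to studying averaging on the validity metric, to comparing many learners and to identifying best features on the same 30 people, and the one protection it explains addresses a different problem. A hypothesis-generating aim lowers the severity. It does not make an optimistic correlation a fair answer to a validity question.

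**Conclusion.** The point holds in conditional form, as a change that should be made. If the best learner, feature set or averaging scheme is picked on the folds that score it, the reported performance is biased upward even with participant-wise folds and in-fold feature selection. Under a pure null the best r averages about 0.31 to 0.34 and passes 0.361 in roughly 40% to 48% of runs, against a mean at or slightly below zero with full nesting.

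The size depends on the assumed 50 to 200 features, 40 pipelines and absence of signal. The direction does not depend on those counts. Where real signal exists the inflation may differ, and it was not simulated. The calculation shows what picking a winner on the scoring folds would do. It does not show that the investigators will do so.

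**What to change.** State that scaling, feature selection or principal components, averaging scheme, tuning and choice of learner are all carried out inside each participant-wise training set, and that the outer participant folds are used only for scoring.

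In reporting:
- give how often each feature is selected across the outer folds, in place of a single best list;
- report all pipelines and averaging schemes tried;
- label any best-of-many result as exploratory and optimistic.

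Naming one primary pipeline per target before the features are linked to the MDS-UPDRS is an acceptable alternative, not a requirement.

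No new participants, visits or data are needed. The cost is computing time, a few sentences in the plan and a lower headline accuracy.

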### Outcomes

The research questions that this study addresses are:

Are the multimodal measurements collected by mobile phones and wearable devices valid for estimating PD symptoms?What extracted information/features from raw data are predictive of MDS-UPDRS scores using data collected by mobile phones and wearables?Are mobile phones and wearable devices usable and accepted for data collection?

These research questions entail collecting data from devices at participants’ home and reference data in-clinic and developing algorithms to associate the MDS-UPDRS score from the data collected at home. The questions also imply measuring compliance to the data regime protocol, usability of the technology and long-term acceptance.

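### The features that answer research question 2 are selected in 30 participants, and no check is stated that they would be selected again

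*Protocol article*

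**What the plan says.** The second research question in the Outcomes section is: "What extracted information/features from raw data are predictive of MDS-UPDRS scores using data collected by mobile phones and wearables". The answer comes in the Data analysis plan, under validity of measurements, where feature selection is to be run and "the best predictive features will be identified". Four selection methods are named for exploration (a relevance, redundancy and complementarity trade-off; mRMR; correlation-based selection; recursive feature elimination), together with principal component analysis. Targets are summative MDS-UPDRS scores and specific items.

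Cross-validation has one stated purpose: "To assess the performance of different machine learning algorithms, k-fold cross-validation" and leave-one-participant-out validation are to be used. No measure of how stable the selected features are is given, and no rule for combining results across methods or targets.

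The Study design section plans the "recruitment of 30 participants with clinically diagnosed PD". The number rests on precedent ("Guided by similar studies that have used between 10 and 50 participants"), and "the goal of this study is towards hypothesis generation and assessing feasibility". Sample size is listed as a limitation; feature stability is not mentioned.

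**The concern.** Performance and selection are separate questions. Cross-validation by participant can give an honest error for a model while the features behind it change from sample to sample, particularly when many candidates compete and the sample is small. Because research question 2 is about the features, a good cross-validated error does not answer it.

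What is at stake is what the study hands on. A later study would take its hypotheses from these features. If some are chance and nothing in the report separates better-supported features from weaker ones, the later study inherits the mixture without knowing it.

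**Working it through.** The article gives no power, effect size or precision figure, so there is none to reproduce. The check asks how far selection at this sample size can be trusted.

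**Inputs from the article.** 30 participants; MDS-UPDRS at two visits, so at most 2 × 30 = 60 target values from 30 independent people.

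**Inputs assumed.** 50, 100 or 200 candidate features; 10 truly related to the score, each with correlation r; the ten with the largest absolute correlation kept; one score per person. Correlation ranking is a simple stand-in for the named methods.

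**Is 50 or more candidates plausible?** The Data collection section lists six hold-the-phone conditions (two hands × three positions), three vowels, two drawings, finger tapping and TUG: 6 + 3 + 2 + 1 + 1 = 13 sources. If all are kept before and after medication, with three actigraphy targets (tremor, bradykinesia, sleep): 13 × 2 + 3 = 29 signals, and 58 features at two per signal. If vocalisation is not split by medication state: 10 × 2 + 3 + 3 = 26 signals, and 52 features.

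**Chance level at n = 30.**
- Two-sided 5% threshold: |r| = t/√(t² + 28) with t = 2.048, which gives 0.361.
- 95% interval for an observed r of 0.40: tanh(atanh 0.40 ± 1.96/√27) = 0.05 to 0.66.
- Chance of at least one false result below 5% among independent null features: 1 − 0.95^50 = 92% for 50 candidates, 99% for 100, over 99.9% for 200.
- Median largest |r| among the unrelated features, simulated: about 0.44, 0.48 and 0.51. The best chance feature typically looks stronger than a true r of 0.4.

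**Simulation.** For a related feature, X = r·y + √(1 − r²)·e; otherwise X is pure noise. 1,000 pairs of independent samples of 30 were drawn per scenario. Results for 50 / 100 / 200 candidates:

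| True r | Chance share of the ten | Shared by two studies |
|---|---|---|
| 0.4 | 30 / 42 / 50% | 50 / 36 / 26% |
| 0.5 | 18 / 24 / 30% | 68 / 58 / 49% |
| 0.6 | 7 / 11 / 15% | 86 / 79 / 73% |

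The sharing follows from the chance share. At r = 0.4 with 100 candidates, each real feature is kept with probability 0.58 and each of the 90 others with probability 4.2/90. Expected sharing is 10 × 0.58² + 90 × (4.2/90)² = 3.36 + 0.20 = 3.6 of ten, as simulated.

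A further run at r = 0.4 gave sharing of 5.0 / 3.6 / 2.7 of ten. Correlating features in blocks of five changes little (r = 0.4: 30 / 42 / 50% chance). With 200 participants and the same 10 true features, the chance share rounds to 0% and sharing to 100%, so in this setting the instability comes from n = 30.

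**Agreement between methods on the same data** (100 candidates, r = 0.4): correlation ranking and recursive elimination agree on 5.2 of ten; with mRMR added, all three agree on 4.9. The first method named in the article was not simulated.

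**A hard cut-off, tested.** Keep only features selected in at least 60% of participant bootstraps (r = 0.4; 50 / 100 / 200 candidates):

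| | Ten best | 60% rule |
|---|---|---|
| Real share of the list | 68 / 58 / 50% | about 79 to 85% |
| Real features kept, of 10 | 6.8 / 5.8 / 5.0 | 4.4 / 3.1 / 1.8 |
| Share of list shared by two studies | 50 / 36 / 27% | 36 / 27 / 17% |

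The rule gives a purer list but loses 5.6 / 6.9 / 8.2 of the ten real features, and recurrence falls.

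**The case against.** The strongest reply is that this rests on what a condensed article does not say. Resampling details are commonly left to a full plan, and feature selection stands in the same paragraph as leave-one-participant-out validation, so selection may be repeated inside the folds. That stands in part: the text neither states nor excludes it. It does not settle the point, because in-fold selection protects the performance estimate. Any two leave-one-out training sets share 28 of their 29 participants, so lists from them look alike by construction and say little about a new sample.

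Second, a reader might infer that one list will be reported. The document does not support that: several methods and targets are named, and comparing methods could itself show agreement. No rule for doing so is given.

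Third, a reader might infer that most of the features would be chance or would not recur. That depends on assumed figures. At r = 0.6, 73% to 86% recur, and mapping items to specific tests may shrink the candidate set for those targets. Against this, the Introduction cites only weak to moderate correlations in an earlier smartphone study done in clinic, and the plan's own preliminary analysis found a correlation only after many participants were removed. Exclusion at H&Y 3 and above also narrows the severity range, which tends to lower correlations. The weaker scenarios are therefore credible, but not established.

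Fourth, the study is declared hypothesis-generating and admits its sample size as a limitation. This stands, and it rules out saying that research question 2 would receive a wrong answer. It does not remove the value of showing which candidates are better supported.

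**Conclusion.** The point holds in a limited form. The article promises the best predictive features from 30 participants as the answer to a research question, and the only validation it states concerns algorithm performance. Under the assumptions above, at r = 0.4, about 30% to 50% of ten selected features are chance and about 2.7 to 5 of ten are shared by two identical studies; at r = 0.6 the chance share is about 7% to 15%. The number of candidates, the number of real features, their strength and the list length are all absent from the document, so the size is uncertain. The change is worth making because it needs no new data and improves what is passed to the next study.

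**What to change.** In the feature selection paragraph of the Data analysis plan, add that:
- each named selection method will be repeated, for each target, in bootstrap or half-sample resamples of whole participants (for example 200), keeping all of a person's records and both MDS-UPDRS assessments together;
- each feature's selection frequency will be reported by method, with highly correlated features counted as a group;
- the selected features will be presented as ranked candidates for confirmation, with these frequencies, and not as established predictors.

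Do not add a hard cut-off that relabels the remaining features as chance. For a hypothesis-generating study, the 60% rule loses too many real features and does not improve recurrence.

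The cost is analysis-plan wording, modest computing time and a more cautious answer to research question 2. Frequencies grade the support for each feature within this sample; they do not replace confirmation in a second one.

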#### Compliance, usability and acceptance

Participants’ compliance is measured using activity logs from which we can derive the number of tests performed and questionnaires answered.

Usability and long-term acceptance of the app will be assessed by computing descriptive statistics about the quantitative answers given to the questionnaires and performing a thematic analysis of the interviews based on the theoretical foundations that defined the questions.

